## Abstract

**Background:**

The prognosis for patients with cervical or endometrial cancer has improved over the last decades. Thus, reducing therapy-related toxicity and impact on quality of life have become more and more important. With the development of new radiotherapy techniques like IMRT (Intensity-modulated radiotherapy) the incidence of acute and chronic toxicities has already been reduced. Nevertheless, rates of complications requiring medical treatment range from 0.7–8% according to literature. 7.7% of patients develop severe complications after 5 years with an increasing risk for complications of 0.3%/year. Particularly, the volume of the small and large bowel receiving low doses (15 Gy) has been shown to be a predictive factor for the development of higher bowel toxicity. With the introduction of proton therapy into clinical practice, there are new opportunities for optimization of organ at risk-sparing thus possibly reducing toxicity.

**Methods/design:**

The APROVE study is a prospective single-center one-arm phase-II-study. Patients with cervical or endometrial cancer after surgical resection who have an indication for postoperative pelvic radiotherapy will be treated with proton therapy instead of the commonly used photon radiation. A total of 25 patients will be included in this trial. Patients will receive a dose of 45–50.4 GyE in 1.8 GyE fractions 5–6 times per week using active raster-scanning pencil beam proton radiation. Platinum-based chemotherapy can be administered if indicated. For treatment planning, rectum, sigma, large and small bowel, bladder and femoral heads are defined as organs at risk. The CTV is defined according to the RTOG consensus guidelines.

**Discussion:**

The primary endpoint of the study is the evaluation of safety and treatment tolerability of pelvic radiation using protons defined as the lack of any CTC AE Grade 3 or 4 toxicity. Secondary endpoints are clinical symptoms and toxicity, quality of life and progression-free survival. The aim is to explore the potential of proton therapy as a new method for adjuvant pelvic radiotherapy to decrease the dose to the bowel, rectum and bladder thus reducing acute and chronic toxicity and improving quality of life.

**Trial registration:**

Registered at https://clinicaltrials.gov, ClinicalTrials.gov Identifier: NCT03184350, registered 09 June 2017, enrolment of the first participant 19 June 2017.

## Background

Cervical cancer was once one of the most common causes of cancer death for women. With the implementation of regular screenings including Pap smear rates of cervical cancer have fallen by 75% in the United States [1]. Nowadays, cervical cancer contributes nearly 8% of all cancers in women worldwide [2]. The American Cancer Society estimates about 12,820 new cases of invasive cervical cancer for 2017 [3]. Treatment of cervical cancer depends very much on stage at time of diagnosis. Early stages are mostly treated with surgery, whereas patients with FIGO stage IIb or higher should be treated with definitive radiochemotherapy. There are also cases where postoperative radiotherapy is indicated to reduce the risk of tumor recurrence [4, 5]. Risk factors for local recurrence are positive resection margins, positive lymphonodal status, >1/3 stromal invasion, capillary lymphatic space involvement, and large clinical tumor diameter. In these cases, postoperative radiotherapy can improve local-recurrence-free survival from 79 to 88% [5], however resulting in higher toxicity rates than after surgery alone. Further studies showed that simultaneous radiochemotherapy is superior to radiation alone both in the adjuvant [6] and definitive setting [7]. For example, Morris et al. could show improved progression-free survival (80% vs. 63%) as well as overall survival (81% vs. 71%) after combined platinum-based radiochemotherapy compared to radiotherapy alone [8].

Endometrial cancer contributes nearly 5% of all cancers in women worldwide [2]. In Europe and the United States, it is the most common cancer of the female reproductive organs. The American Cancer Society estimates about 61,380 new cases of endometrial cancer for 2017 [3]. Most patients with endometrial cancer are diagnosed in an early stage resulting in a low cancer specific mortality. Primary treatment consists of radical surgery. The prognosis of patients with endometrial cancer depends very much on tumor stage, grading, histology, depth of myometrial invasion, capillary lymphatic space involvement and age. All patients with clear-cell or serous adenocarcinoma histology should receive postoperative percutaneous pelvic radiotherapy. But also patients with endometroid adenocarcinoma FIGO stage Ib or higher and presence of risk factors should receive postoperative radiotherapy [9–11].

Therapy-associated toxicity is the limitating factor for adjuvant pelvic radiotherapy. Recurrence of the vaginal cuff is the most common site of locoregional recurrence for patients with endometrial cancer. With the use of endovaginal brachytherapy, sufficiently high doses for a good local control can be achieved with better sparing of organs at risk than with external beam radiotherapy alone [11]. New technical developments in the field of radiotherapy like IMRT (intensity-modulated radiotherapy), VMAT (volumetric arc therapy) and Tomotherapy have resulted in better sparing of organs at risk (OARs) like rectum, bowel and bladder thus reducing toxicity of pelvic radiotherapy. Nevertheless, rates of complications requiring medical treatment range from 0.7–8% according to literature [12–15]. Especially chronic side effects have a high impact on patients’ quality of life. In a trial with 1784 patients receiving definitive radiotherapy for FIGO stage Ib cervical cancer, 7.7% developed severe complications after 5 years. The risk for developing complications increased for 0.3% per year resulting in an actuarial 20-year-complication rate of 14%. Side effects most commonly consist of gastro-intestinal/gastro-urogenital symptoms like proctitic symptoms, bleeding, fistula, ulcers, hematuria or vaginal ulcers and fistulas [16]. The rate of toxicities correlates with dose per fraction, cumulative dose as well as the volume of the organ at risk affected by radiotherapy. A recent study by Chopra et al. showed that particularly the extent of the bowel being exposed to low doses is a crucial factor for the development of chronic gastrointestinal toxicities [17]. The volume of the bowel receiving less than 15 Gy could be identified as an independent predictive factor for the development of > grade 3 chronic intestinal toxicities. The volume of the small bowel and large bowel receiving 15 Gy or less should be restricted to <257cm^3^ and <250cm^3^, respectively, to avoid late side effects [17].

In the last decade, the use of particles for radiation of certain tumors has found its way into clinical practice. Proton therapy with its characteristic Bragg peak allows for a more precise radiation with better sparing of OARs thus possibly reducing radiation related toxicities. This facilitates dose escalation, particularly in patients receiving combined-modality therapy, for which toxicity is enhanced. A planning study from 2012 could demonstrate that the use of passive scattering proton therapy (PSPT) or intensity-modulated proton therapy (IMPT) resulted in a statistically significant decrease in dose to the small and large bowel and kidneys, while maintaining excellent planning target volume coverage [18]. Lin et al. published a study in 2016 of 11 patients with post-hysterectomy gynecologic cancer who received pencil beam scanning proton radiation therapy (PBS) to the whole pelvis. One patient (9%) developed grade 3 acute gastrointestinal toxicity, no patient developed ≥ grade 3 genitourinary toxicity. The volume of pelvic bone marrow, bladder, and small bowel receiving 10 to 30 Gy was significantly lower with PBS than with IMRT with good coverage of the target volume [19].

Previous work of our group included plan comparisons of IMRT and PBS proton therapy plans based on CT-scans obtained for radiation treatment planning of patients with cervical or endometrial cancer. It could be shown that with the use of active raster scanning PBS proton radiation the V15 of the bowel could be reduced effectively compared to the IMRT plans (unpublished data).

The aim of this prospective study is to evaluate safety and treatment tolerability of pelvic radiation using protons and to explore if reduced dose to the OARs results in clinically apparent reduced side effects and mitigates the influence of pelvic radiation on quality of life. All in all, we aim to assess the potential of proton therapy as a new method for adjuvant pelvic radiotherapy to decrease the dose to the bowel, rectum and bladder thus reducing acute and chronic toxicity and improving quality of life.

## Methods/design

### Study design

The study is designed as a prospective single-center one-arm phase-II-trial evaluating the clinical feasibility and toxicity of postoperative pelvic radiation using proton therapy. Patients fulfilling the inclusion criteria will be treated with active raster scanning proton radiation up to total doses of 45.0–50.4 GyE in 1.8 GyE single dose fractions. 25 patients are planned to be enrolled in a time period of 2 years.

### Study objectives

The primary objective of the trial is the assessment of safety and treatment tolerability defined as the lack of any CTC AE ≥ grade 3 gastrointestinal or urogenital toxicity or premature treatment abortion.

Secondary endpoints are clinical symptoms and toxicity according to the CTC AE version 4.0. criteria, quality of life assessed with the EORTC-QLQ30/−EN24/−CX24 questionnaires and progression-free survival.

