### Sample size calculation and statistical analysis

The APROVE trial is a prospective single-center one-arm phase-II-study. Primary endpoint is the evaluation of safety and treatment tolerability of pelvic radiation using proton beam radiotherapy. 25 patients will be included in the study. Sample size calculation was performed to demonstrate a treatment tolerability rate higher than 80% with a power of 1-β = 0.90 using a binomial test at a one-sided significance level of α = 0.1 under the assumption of an actual treatment tolerability rate of 0.96. The primary analysis includes all enrolled patients. In addition, a per-protocol analysis will be performed. For the primary endpoint, a point estimate for the tolerability rate will be calculated alongside a one-sided 90- and 95%- confidence interval. Methods of descriptive data analysis will be used to evaluate the secondary endpoints and safety data. This includes calculation of appropriate measures of the empirical distribution and graphical display of the results.

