### Duration of the study

The primary objective of the study is to prove good treatment tolerability of pelvic radiation using proton beam radiotherapy, defined as the non-occurrence of CTC grade 3 gastrointestinal or urogenital toxicities during radiotherapy and up to 3 months after its completion. To assess the primary endpoint, the final study visit will be 3 months after the last patient completed the radiotherapy. The study ends 2 years after the last patient was treated. Recruitment of the patients is planned over a time period of 2 years.

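### The primary endpoint is stated inconsistently on two points: whether stopping treatment early is a failure, and whether toxicity outside the gastrointestinal and urogenital systems counts

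*Protocol article*

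**What the plan says.** The article gives the content of the primary endpoint in three places.

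- **Study objectives (Methods):** "lack of any CTC AE ≥ grade 3 gastrointestinal or urogenital toxicity or premature treatment abortion". Toxicity is limited to two organ systems, early stopping counts, and no time window is given. General toxicity by CTC AE 4.0 is listed in the same section as a secondary endpoint.
- **Duration of the study (Methods):** "non-occurrence of CTC grade 3 gastrointestinal or urogenital toxicities during radiotherapy and up to 3 months after its completion". The organ limit is the same and a window is given, but early stopping is not mentioned.
- **Abstract, Discussion paragraph:** "defined as the lack of any CTC AE Grade 3 or 4 toxicity". There is no organ limit, no early-stopping component and no window.

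The section on sample size and statistical analysis does not choose between them. It says only "Primary endpoint is the evaluation of safety and treatment tolerability of pelvic radiation using proton beam radiotherapy". That section plans for n = 25, sized "under the assumption of an actual treatment tolerability rate of 0.96", against a null rate of 80%, with a one-sided binomial test at level 0.10 and power 0.90. Every enrolled patient is to be counted in the primary analysis.

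**The concern.** The trial's only hypothesis test rests on one count: how many of 25 patients tolerated treatment. That count is reproducible only if the failure criterion is the same wherever it is stated. Here two components change from section to section, and both can affect patients this trial will enrol.

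- **Early stopping.** A patient who stops protons early without grade 3 or higher toxicity stays in the denominator, because all enrolled patients are analysed. She is a failure under Study objectives and a success under Duration of the study and the abstract.
- **Organ scope.** Platinum-based chemotherapy is allowed, and the monitoring section lists haematological toxicity, fatigue and skin toxicity among the acute effects to be expected. A patient whose only grade 3 event is haematological is a failure under the abstract and a success under both Methods sections.

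At stake is whether a reported tolerability rate, and the pass or fail drawn from it, has one meaning. It is also unclear which endpoint the planning rates of 0.80 and 0.96 describe. If a wider definition adds any failures, 0.96 cannot be the true rate for both the wider and the narrower one.

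**Working it through.** **Step 1. The definitions side by side**

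| Element | Study objectives | Duration of the study | Abstract |
|---|---|---|---|
| Organ systems | GI or urogenital | GI or urogenital | any |
| Grade wording | 3 or higher | 3 | 3 or 4 |
| Early stopping is a failure | yes | not mentioned | not mentioned |
| Window | none given | to 3 months after radiotherapy | none given |

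**Step 2. Reproduce the sample size**

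Inputs, all from the sample size section: n = 25, p0 = 0.80, p1 = 0.96, one-sided α = 0.10, target power 0.90.

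For an exact binomial test, take the smallest r with P(X ≥ r | n, p0) ≤ 0.10. Power is then P(X ≥ r | n, p1).

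At n = 25:

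- r = 22: P(X ≥ 22 | 0.80) = 0.234, which is above 0.10
- r = 23: P(X ≥ 23 | 0.80) = 0.0982, which is within 0.10
- power at r = 23: P(X ≥ 23 | 0.96) = 0.9235

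For n from 15 to 24, power never exceeds 0.839 (at n = 18), so 25 is the first size in that range to reach 0.90. The planned number reproduces. The implied rule is success at 23 or more of 25, that is, at most two failures. The article does not state this cut-off; it follows from the inputs.

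**Step 3. What reclassification does under that rule**

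| Tolerating patients | Exact p against 0.80 | Result |
|---|---|---|
| 25/25 | 0.004 | success |
| 24/25 | 0.027 | success |
| 23/25 | 0.098 | success |
| 22/25 | 0.234 | no success |

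- At the boundary, one patient classified differently (23 to 22) reverses the conclusion. If the true rate is 0.96, the chance of landing on exactly 23 is P(X ≥ 23) − P(X ≥ 24) = 0.9235 − 0.7358 = 0.188.
- From 25/25, three patients are needed. Three who stop early without grade 3 or higher toxicity give 22/25 under Study objectives and 25/25 under the other two statements. Three with isolated grade 3 haematological toxicity give 22/25 under the abstract and 25/25 under both Methods sections.

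**Step 4. Illustration only: power if the definition lowers the true rate**

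P(X ≥ 23 | n = 25, p), with p0 kept at 0.80:

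| True rate p | Power |
|---|---|
| 0.96 | 92.4% |
| 0.94 | 81.3% |
| 0.92 | 67.7% |
| 0.91 | 60.6% |
| 0.86 | 30.0% |

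Only 0.96 comes from the article. The lower rates are assumed.

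**The case against.** The strongest reply is that the Methods are largely reconcilable and that the abstract merely compresses them. Much of this stands.

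- **Window.** Duration of the study exists to fix timing and ties assessment of the primary endpoint to the 3-month visit. It can fairly be read as supplying the window that Study objectives leaves out.
- **Grade.** Grade 3 without a sign for higher grades is most likely shorthand. Read literally, it would count a patient with grade 4 bowel toxicity as having tolerated treatment, which cannot be intended.
- **Organ scope.** The two Methods sections agree on it, and Study objectives already places general toxicity among the secondary endpoints. A reader who trusts the Methods over the abstract has an answer for the haematological case.

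A reader might therefore go too far in calling these three incompatible definitions; the grade and window differences do not support that. A reader might also infer that the definition is open to choice once the data are known. The article reports a final protocol approved by an ethics committee and an expert group. That document is not shown, so nothing here establishes that the choice is open. Nor do the lower power figures measure the cost of the inconsistency. Their failure rates have no source in the article, and they hold the 0.80 null fixed while the endpoint changes.

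Two things are not answered. Both Methods sections define the primary objective, and they disagree on whether early stopping is a failure; setting the abstract aside does not remove this. The abstract's organ scope also differs in substance from the Methods, and a condensed text that defines the endpoint should not widen it.

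**Conclusion.** The inconsistency is real and limited to two substantive points: the early-stopping component, which appears only in Study objectives, and the organ restriction, which is missing from the abstract. Grade wording and the time window are lesser points to tidy at the same time. The sample size arithmetic is correct; the defect is that the tested rate is not tied to one definition.

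With at most two failures allowed among 25, one differently classified patient decides the result at the boundary and three decide it from a perfect count. This rests on the derived cut-off of 23 and on such patients occurring; the article gives no frequency for either type. No specific loss of power can be claimed.

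**What to change.** Use one definition in the abstract, Study objectives and Duration of the study, and refer to it in the sample size section. One version that uses only what the article already contains takes the components in Study objectives (GI or urogenital toxicity of grade 3 or higher, or early stopping of treatment) and adds the window in Duration of the study (from the start of radiotherapy to 3 months after it ends).

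Three details should be settled with it:

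1. State whether the end of radiotherapy means the last proton fraction or the brachytherapy boost, which the Radiation therapy section places in the following week. The start of the 3-month count depends on this.
2. Report toxicity of other organs, including haematological, as secondary safety data, as Study objectives already provides.
3. Confirm that 0.80 and 0.96 were set for this composite, and state the success rule of 23 or more of 25.

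The cost is a wording amendment, with no extra patients or visits. The exception is the third item: if the planning rates were set for toxicity alone, the sample size calculation must be repeated with rates for the composite.

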### Trial organization and coordination

The APROVE study has been designed by the study initiators at the Department of Radiation Oncology in cooperation with the Institute of Medical Biometry and Informatics at the University Hospital Heidelberg. The study is carried out by the Department of Radiation Oncology in cooperation with the Heidelberg Ion beam Therapy-center. Statistical analysis is performed by the Institute of Medical Biometry and Informatics at the University of Heidelberg. The overall coordination is performed by the Department of Radiation Oncology at University Hospital Heidelberg. This department is also responsible for the overall trial management, database management, quality assurance including monitoring and reporting.

### Investigators

The study investigators are experienced radiation oncologists specialized in the treatment of patients with gynecologic malignancies. Patients will be recruited and treated by the physicians of the Department of Radiation Oncology of the University Hospital Heidelberg.

### Ethics, informed consent and safety

The final protocol was approved by the ethics committee of the University of Heidelberg, Heidelberg, Germany (Nr: S-155/2016) and by an independent expert group of the German Society for Radio-oncology (DEGRO). This study complies with the Helsinki Declaration in its recent German version, the principles of Good Clinical Practice (GCP) and the Federal Data Protection Act. The trial will also be carried out in keeping with local legal and regulatory requirements. The medical secrecy and the Federal Data Protection Act will be followed. The ClinicalTrials.gov Identifier is NCT03184350.

### Data handling, storage and archiving of data

All findings including clinical and laboratory data will be documented by the investigator or an authorized member of the study team in the subject’s medical record and in the case report form (CRF). The data will be stored and archived according to the §13 of the German GCP-Regulation and §28 c of the German X-Ray Regulation (StrlSchV) for at least 30 years after the trial termination.

### Patient selection

Inclusion criteria according to the protocol are:Histologically confirmed cervical or endometrial cancerIndication for postoperative radiotherapyKarnofsky Index ≥70Age between 18 and 80 yearsWritten informed consent

Exclusion criteria are the following:patients refusal or incapability of informed consentimplanted active medical devices lacking approval for ion beam radiationmetallic implants in the radiation field, e.g. hip prosthesesprior pelvic irradiationparticipation in another clinical trial which might influence the results of the APROVE trial

Simultaneous chemotherapy is NOT an exclusion criterium.

### Sample size calculation and statistical analysis

The APROVE trial is a prospective single-center one-arm phase-II-study. Primary endpoint is the evaluation of safety and treatment tolerability of pelvic radiation using proton beam radiotherapy. 25 patients will be included in the study. Sample size calculation was performed to demonstrate a treatment tolerability rate higher than 80% with a power of 1-β = 0.90 using a binomial test at a one-sided significance level of α = 0.1 under the assumption of an actual treatment tolerability rate of 0.96. The primary analysis includes all enrolled patients. In addition, a per-protocol analysis will be performed. For the primary endpoint, a point estimate for the tolerability rate will be calculated alongside a one-sided 90- and 95%- confidence interval. Methods of descriptive data analysis will be used to evaluate the secondary endpoints and safety data. This includes calculation of appropriate measures of the empirical distribution and graphical display of the results.

### Investigation schedule

#### Indication

The oncological treatment concept for each patient is based on interdisciplinary assessment following approved standard therapies and guidelines. The adjuvant treatment is defined after surgery and complete staging including thoraco-abdominal CT scan and pelvic MRI scan. This allows for histologically confirmed diagnosis, classification and staging.

According to institutional policies the following patients receive whole pelvic radiotherapy:

Cervical cancer patients: All patients with FIGO stage ≥ IIb, N+ or positive resection margins and no possibility of further resection. Furthermore, patients with FIGO stage < IIb and a combination of risk factors like lymphangiosis carcinomatosa (L1), deep stromal invasion, tumor size >4 cm (according to the Sedlis criteria [5] and the german S3-guidelines).

Endometrial cancer patients: All patients with serous, clear cell or undifferentiated histology and all patients with endometroid, mucinous or adenosquamous carcinomas FIGO stage ≥ III. Furthermore, patients with FIGO stage I/II according to the ESMO-ESGO-ESTRO Consensus Conference on Endometrial Cancer [20] taking into account lymphadenectomy and risk factors such as lymphovascular invasion, depth of myometrial invasion, grading and patient age (according to the risk classification developed by the PORTEC and GOG groups).

In general, every patient with an indication for percutaneous pelvic radiotherapy also receives a high dose rate (HDR)-vaginal brachytherapy (VBT)-boost.

